**Methods/design:**

A total of 138 eligible participants with KOA who consent to participate will be randomly divided into Groups A, B, and C in a ratio of 1:1:1. Participants in Group A will receive verum acupuncture and placebo gel, while those in Groups B and C will be treated with diclofenac diethylammon gel and sham acupuncture, sham acupuncture and placebo gel, respectively. The patients will receive 4 weeks of treatment, five times a week, including acupuncture treatment once a day for 30 min and gel treatment three times a day. The primary outcome will be the change of Western Ontario and McMaster Universities Osteoarthritis Index (WOMAC) at week 4. The secondary outcomes will include visual analog scale (VAS), Arthritis Quality of Life Measurement Scale Simplified Scale (AIMS2-SF), Beck Anxiety Inventory (BAI), Beck Depression Inventory (BDI) and Credibility/Expectancy Questionnaire. The evaluation will be performed at baseline, week 4, 8, and 12 after randomization.

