### Sample size

Power Analysis and Sample Size (PASS, provided by Shanghai Datanine Software Co., Ltd., China) was used for sample size calculation. Based on prior studies and clinical experience, we expected the WOMAC total score to decrease by 17 points after acupuncture, a reduction by 13 points after diclofenac diethylammon gel, and a reduction by 10 points in the placebo group [32, 33]; the standard deviation is 10.24. The type I error inflation can be avoided by setting the significance level at 0.05 on a two-sided basis. Forty-two participants in each group will have 80% power to detect significant differences between the groups. The sample size was increased to 46 participants in each group to supplement for a possible 10% loss at follow-up. So, this trial will include 138 participants in total.

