### Primary outcome

The Western Ontario and McMaster Universities Osteoarthritis Index (WOMAC) [34] will be the primary outcome measure for this trial. The WOMAC is an osteoarthritis questionnaire with high reliability and validity that has been widely used in various clinical trials involving KOA patients [35]. WOMAC includes 5 pain-related items, 2 stiffness-related items, and 17 physical function-related items, each item is scored on a scale of 0–10, and the total score is on a scale of 0–240, with higher scores indicating more severe KOA symptoms in patients [36]. Outcome assessor will assess participants at baseline, week 4, week 8 and week 12, but the primary outcome will be the assessment at week 4.

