### Statistical analysis

The statistical analysis procedure of this trial will be performed using SPSS 22.0 software (IBM Corporation, Armonk, NY, USA). Statisticians responsible for data analysis will be independent of the research team and blind to the test settings. The data will be tested for normality using the quantile–quantile plots. We will analyze the data from WOMAC, VAS, AIMS2-SF, BAI, and BDI within the group and use paired-sample t-tests for those data that follow normal distributions, and in the case of data that did not conform to the normal distribution, Wilcoxon test will be used. Age, height, weight, and outcome assessments will be compared among the three groups, the one-way analysis of variance (ANOVA) will be applied to data conforming to a normal distribution, and the Kruskal–Wallis one-way ANOVA will be used to analyze data that do not follow a normal distribution. Intention-to-treat analysis will be used for outcome measurements to analyze missing values, based on the last observation carried forward method. In the analysis of missing values, only patients who attended at least 80% of the sessions and completed the follow-up in the allocated intervention group will be included. In addition, data will be tested by bilateral tests, and the confidence intervals are all 95% bilateral; *p* < 0.05 (*α* = 0.05) is considered to indicate statistical significance.

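### The among-group test is unadjusted one-way ANOVA or Kruskal–Wallis: valid, but less efficient than ANCOVA on the baseline WOMAC already collected, and it leaves the primary variable and test open

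*Protocol article*

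**What the plan says.** The Statistical analysis section gives one procedure for all among-group comparisons: "Age, height, weight, and outcome assessments will be compared among the three groups". For these, "the one-way analysis of variance (ANOVA) will be applied to data conforming to a normal distribution", and otherwise "the Kruskal–Wallis one-way ANOVA will be used to analyze data that do not follow a normal distribution". The choice rests on a graphical check: "The data will be tested for normality using the quantile–quantile plots". No covariate or adjusted model is named anywhere in the article. Baseline values of the outcomes are used explicitly only in the within-group paired tests, which do not compare treatments.

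Baseline data are available. Table 1 schedules WOMAC, VAS, AIMS2-SF, BAI and BDI at baseline and at weeks 4, 8 and 12.

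The primary variable is worded in two ways. The abstract says: "The primary outcome will be the change of Western Ontario and McMaster Universities Osteoarthritis Index (WOMAC) at week 4". The Primary outcome section says: "Outcome assessor will assess participants at baseline, week 4, week 8 and week 12, but the primary outcome will be the assessment at week 4". The Sample size section plans in terms of reductions ("we expected the WOMAC total score to decrease by 17 points after acupuncture", 13 points with diclofenac gel, 10 with placebo) with an SD of 10.24. It does not say whether that is the SD of change or of the week-4 score.

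**The concern.** Three linked weaknesses follow from this wording.

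- **Efficiency.** An outcome with a measured baseline gets the same unadjusted test as age and height. A week-4 comparison ignores baseline. A change-score comparison uses it, but with the coefficient fixed at 1 instead of estimated.
- **Chance imbalance.** With 46 per arm some baseline difference will occur. An unadjusted week-4 comparison leaves it uncorrected, and a change-score comparison generally over-corrects it.
- **Openness.** ANOVA of change and ANOVA of the week-4 score can give different estimates and p-values from the same data, and the article does not say which is primary. The choice between ANOVA and Kruskal–Wallis waits for the data, with no stated criterion for reading the plots. Kruskal–Wallis also gives no mean difference in WOMAC points to set against the planning values.

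At stake are the precision of the primary estimate and having a single primary result fixed in advance.

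**Working it through.** **Inputs.** From Sample size: mean reductions 17, 13 and 10; SD 10.24; two-sided alpha 0.05; 42 evaluable per group. Assumed, because the documents do not give it: the within-group correlation rho between baseline and week-4 WOMAC, taken as 0.3, 0.5 and 0.7. Also assumed: equal variances s² at both visits.

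**1. The plan's own figure.** The grand mean is 13.333. The squared deviations are 13.444 + 0.111 + 11.111 = 24.667. Cohen's f = sqrt(24.667/3)/10.24 = 0.280. The noncentrality is 42 × 24.667/10.24² = 9.88 on 2 and 123 df. Power from the noncentral F is 0.800 with 42 per group and 0.790 with 41. The stated 42 is therefore exactly the size for an unadjusted three-group ANOVA and takes no credit for baseline.

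**2. Residual variances.**
- ANOVA of the week-4 score: s².
- ANOVA of change: 2s²(1 − rho).
- ANCOVA: s²(1 − rho²).

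Relative to the week-4 analysis, the ANCOVA variance is 1 − rho². Relative to the change analysis, it is (1 − rho²)/[2(1 − rho)] = (1 + rho)/2.

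**3. Omnibus power at 42 per group.** The noncentrality becomes 9.88 divided by the variance ratio, on 2 and 122 df (one df spent on the covariate). The unadjusted comparator is 80.0% throughout.

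| rho (assumed) | 10.24 = SD of change: variance ratio | Power | n per group for 80% | 10.24 = SD of week-4 score: variance ratio | Power | n per group for 80% |
|---|---|---|---|---|---|---|
| 0.3 | 0.65 | 94.2% | 28 | 0.91 | 83.8% | 39 |
| 0.5 | 0.75 | 90.5% | 32 | 0.75 | 90.5% | 32 |
| 0.7 | 0.85 | 86.4% | 36 | 0.51 | 98.0% | 22 |

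On the change reading the gain keeps shrinking as rho rises: 84.3% at rho 0.8 (ratio 0.90) and 82.1% at rho 0.9 (ratio 0.95).

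**4. Chance imbalance.** Let d be the observed baseline difference between two arms and b the within-group slope of week-4 on baseline WOMAC (b = rho under equal variances). Given d, the week-4 comparison is off by b × d on average, the change comparison by (b − 1) × d, and ANCOVA by zero if the relation is linear with a common slope. At rho 0.5 the two unadjusted analyses are off by +0.5d and −0.5d, in opposite directions.

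**5. Change or week-4 score.** In a model with group and baseline, replacing the week-4 score by change subtracts baseline from both sides. The baseline coefficient falls by 1 and the group coefficients do not move. With baseline as covariate the two wordings therefore give the same treatment effect.

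**The case against.** The strongest reply is that nothing here is broken. Under 1:1:1 randomisation, ANOVA of either variable is unbiased with valid type I error. The sample size and the analysis agree with each other, and the stated 80% is delivered under the plan's own assumptions. All of that stands. A reader might infer from the missing covariate that the planned analysis is biased or that the trial falls short of its stated power. The documents support neither: the imbalance in step 4 is conditional on the baseline difference observed and averages to zero over randomisations.

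A reader might also infer that baseline is ignored whichever variable is used. That is not so either. If change is analysed, baseline is already partly used, and the abstract and the planning reductions support that reading at least as well as the other.

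On the choice of test, the normality rule is written down in advance, and the analysts are blinded to group (Blinding; Statistical analysis), so it could not readily be steered toward a treatment. This makes it a secondary weakness, but the primary test still depends on a judgement made on the outcome data.

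Finally, the article is condensed and an analysis plan may exist elsewhere. That carries little weight here, because the article itself names the among-group tests and words the primary variable in two ways.

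**Conclusion.** The point holds as an efficiency and prespecification improvement, not as an error that invalidates the analysis. The planned tests are valid but less efficient than ANCOVA on a baseline already collected. They do not properly account for chance imbalance, and the primary variable and test stay open until the data are seen.

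Over the assumed rho of 0.3 to 0.7, residual variance falls by 35% to 15% if 10.24 is the SD of change, or by 9% to 49% if it is the SD of the week-4 score. Omnibus power at 42 per group rises from 80% to between about 84% and 98%. The direction of the gain is secure. Its size is not, because it depends on rho, on equal variances and on what 10.24 measures, none of which the documents give.

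**What to change.** Prespecify one primary analysis: ANCOVA of week-4 WOMAC total on treatment group, with baseline WOMAC total as covariate. Report adjusted mean differences between groups with 95% CIs. Do not make the choice of primary test conditional on Q-Q plots; keep rank-based tests as sensitivity analyses. Use the same model for VAS, AIMS2-SF, BAI and BDI, each with its own baseline. Word the primary outcome identically in the abstract and the Primary outcome section.

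The cost is a change of analysis wording. It needs no new data, visits or patients, and the 138 participants stay as planned, with the gain taken as precision. The Trial status section says recruitment had not begun at the time of writing; the change should in any case be fixed before outcome data are examined.

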**Fig. 1 Fig1:**
[figure not shown]
Flowchart of the trial

**Table 1 Tab1:** Study design schedule

Time point (week)	Baseline		Treatment phase			Follow-up	
	0-week	1-week	2-week	3-week	4-week	8-week	12-week
*Enrollment*							
Eligibility screen	×						
Informed consent	×						
Allocation	×						
Randomization	×						
*Interventions*							
Group A (*n* = 46)		×	×	×	×		
Group B (*n* = 46)		×	×	×	×		
Group C (*n* = 46)		×	×	×	×		
*Assessments*							
WOMAC	×				×	×	×
VAS	×				×	×	×
AIMS2-SF	×				×	×	×
BAI	×				×	×	×
BDI	×				×	×	×
Expectancy questionnaire	×						
*Participants safety*							
Adverse events	×	×	×	×	×	×	×

Qualification screening and informed consent will be completed before the assignment. After allocation, each patient will be treated within 4 weeks. The evaluation will be performed at baseline and weeks 4, 8, and 12, respectively, after randomization. Adverse events will be recorded on the case report form at any time during treatment

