### Discontinuation criteria and modification

Participants who meet the following criteria will be excluded from the trial during the trial period: (1) receiving additional treatments that may interfere with acupuncture's efficacy, violating the protocol, such as taking analgesics without permission or receiving other treatments; (2) participants were reluctant to continue treatments; (3) missing more than 4 of 20 acupuncture treatment sessions; and (4) serious adverse events occurred and doctors consider the trial should be terminated.

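### Carrying the last observation forward to the week-4 primary endpoint can only carry baseline, so any patient imputed this way is scored as exactly zero change

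*Protocol article*

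**What the plan says.** The abstract fixes the endpoint: "The primary outcome will be the change of Western Ontario and McMaster Universities Osteoarthritis Index (WOMAC) at week 4". The Primary outcome section gives the visits: "Outcome assessor will assess participants at baseline, week 4, week 8 and week 12". The note to Table 1 agrees ("The evaluation will be performed at baseline and weeks 4, 8, and 12, respectively, after randomization"), and the WOMAC row of that table is empty for weeks 1 to 3.

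The missing-data rule is in Statistical analysis: missing outcome values are handled under intention-to-treat, "based on the last observation carried forward method". The sentence after it sets a restriction: "In the analysis of missing values, only patients who attended at least 80% of the sessions and completed the follow-up" in the allocated group are to be included.

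The Sample size section plans on WOMAC reductions of 17 points with acupuncture, 13 with diclofenac gel and "a reduction by 10 points in the placebo group", with SD 10.24. It gives 42 per group for 80% power, raised to 46 for a possible 10% loss. The between-group test is a one-way ANOVA across the three arms when data are normal.

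**The concern.** Carrying a value forward needs an earlier value. At week 4 the only earlier WOMAC score is baseline, so the imputed change is zero by construction. Scores at week 8 or 12 cannot be carried backward, so a patient who misses week 4 and then returns is still scored as unchanged.

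The plan expects improvement in every arm, including sham acupuncture with placebo gel. A block of zeros pulls each arm's mean towards 0 in proportion to its missing share, and most in the arm that improves most. With equal loss this dilutes the contrast and costs power. With unequal loss the estimate also depends on who failed to attend, and the false-positive rate can leave 5%.

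The problem is specific to the primary endpoint. At weeks 8 and 12 the rule can at least carry a post-treatment score.

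**Working it through.** **Inputs.** Mean reductions 17 / 13 / 10 (arms A / B / C), SD 10.24, two-sided alpha 0.05, 42 analysed and 46 randomised per arm, 10% loss: all from Sample size. Test: one-way ANOVA, from Statistical analysis. Assumptions not in the protocol: drop-outs would otherwise change like completers in their arm, and the split of loss between arms is as stated in each line below.

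**1. The plan's own figure.** ANOVA noncentrality is λ = n·Σ(mᵢ − m̄)²/SD². Here m̄ = 40/3 = 13.33, the squared deviations sum to 24.67, and SD² = 104.86. With n = 42, λ = 42 × 24.67/104.86 = 9.88 and power is 0.800. The stated 42 per group reproduces as a three-group ANOVA, so that is the right test on which to judge the rule.

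**2. Distance of the imputed value from the planning means.** 10/10.24 = 0.98 SD in arm C and 17/10.24 = 1.66 SD in arm A.

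**3. Effect of zero-scoring.** If a share d of an arm is set to 0:
- mean = (1 − d)·m
- variance = (1 − d)(SD² + m²) − [(1 − d)·m]²

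With d = 0.10 in every arm:
- means are 15.3 / 11.7 / 9.0, so A − C = 6.3 instead of 7.0
- SDs are 10.97 / 10.47 / 10.17, with average variance about 111.1
- squared deviations about 12.0 sum to 3.3² + 0.3² + 3.0² = 19.98
- λ = 46 × 19.98/111.1 = 8.27

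| Analysis at 10% loss per arm | ANOVA power |
|---|---|
| No loss, 46 per arm (reference) | 0.84 |
| Observed patients only, 46 × 0.9 ≈ 41 per arm | 0.79 |
| 46 per arm, missing scored as zero | 0.72 (simulation, 20,000 trials: 0.71) |

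The step from 0.84 to 0.79 is ordinary attrition. The step from 0.79 to 0.72 is the cost of the imputation rule.

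At equal loss of 5% and 20%, A − C becomes 6.65 and 5.6, and zero-scored power is 0.78 and 0.60. These two power figures include ordinary attrition.

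**4. Unequal loss (hypothetical).** A − C = 17(1 − d_A) − 10(1 − d_C).
- 5% in A, 20% in C: 16.15 − 8.00 = 8.15, which is 16% too large (8.15/7 = 1.16).
- 20% in A, 5% in C: 13.60 − 9.50 = 4.10, which is 41% too small (4.10/7 = 0.59).

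**5. Type I error when all arms truly improve by 10 points** (ANOVA, 46 per arm, simulation):
- equal 10% loss: 5.0%
- 5 / 10 / 15% loss in A / B / C: 6.6%
- 5 / 10 / 20% loss: 9.3%

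**The case against.** **Not everyone who misses week 4 need be imputed.** A reader might infer that every such patient is scored as zero. The documents do not establish that. The sentence on attendance and completed follow-up may limit who is imputed, and the Discontinuation section says "Participants who meet the following criteria will be excluded from the trial during the trial period", listing extra treatments, unwillingness to continue and more than 4 missed sessions of 20. On that reading many early drop-outs would be left out of the analysis, not set to zero. This stands as a limit on scope. It does not rescue the rule, because any week-4 value that is carried forward is still baseline. It also exposes a second fault, since the restriction conflicts with intention-to-treat.

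**The planning means are not predictions for drop-outs.** A reader might also infer that the plan itself contradicts zero change in these patients. It does not: 17, 13 and 10 are arm means, and some patients who stop may not improve. What stands against the rule is that the protocol offers no support for zero and treats it as observed data.

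**Bias and excess type I error need unequal loss.** This is correct. The protocol gives one overall rate of 10%, participants are blinded, and the session schedule is the same in all arms. With equal loss the type I error stays at about 5%. The documents do not show that it will be inflated.

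**An analysis plan may settle this.** A consistent one would inherit the rule. The protocol names the method, so this is a stated choice and not missing detail.

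**Conclusion.** The point holds for any patient to whom the rule is applied at week 4: the imputed change is exactly zero, and later WOMAC scores are not used. That follows from the visit schedule alone.

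At the plan's own loss rate, the cost attributable to the rule is about 7 points of ANOVA power, leaving 0.72 where 80% was intended, and a primary contrast diluted by a tenth. This rests on the planning means and SD, loss equal across arms, drop-outs otherwise like completers, and the reading under which all missing week-4 values are imputed.

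Bias in either direction, and a type I error of roughly 7% to 9%, are conditional on assumed unequal loss and should be reported only as such. The common defence that carrying forward is conservative fails in that case: heavier loss in the placebo arm enlarges the apparent effect. The matter should be changed before analysis, but it does not invalidate the design.

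**What to change.** 1. For the primary analysis, replace the carry-forward rule with a mixed model for repeated measures on WOMAC at weeks 4, 8 and 12, with group, visit, group-by-visit and baseline WOMAC, taking the week-4 group contrasts as the primary estimate. Patients with no post-baseline score contribute nothing to this model. Multiple imputation that uses baseline and the week-8 and week-12 values is the alternative, and it also covers those patients.
2. Add one delta-adjusted sensitivity analysis whose range includes zero change for drop-outs. The possibility that they do not improve is then tested openly.
3. Reconcile the restriction on attendance and completed follow-up with intention-to-treat by making it a separate per-protocol analysis, and state who belongs to each analysis set.

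The cost is revised wording and a little more programming. All the visits are already scheduled, so no new data are needed, and the Trial status section says recruitment had not begun.

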## Methods and analysis

### Study design

This is a double-dummy RCT that aims to compare the analgesic efficacy of acupuncture, diclofenac diethylammon, and placebo in the treatment of KOA, which will conduct research and write research reports in accordance with the CONSORT recommendations for reporting randomized trials. Based on clinical criteria developed by the American College of Rheumatology (ACR) [29], 138 patients with KOA will be recruited. The ratio of 1:1:1 will be used to randomize all patients after informed consent is obtained, which are Group A: verum acupuncture group (verum acupuncture and placebo gel; verum acupuncture is traditional acupuncture, a technique for treating diseases by stimulating acupoints with acupuncture); Group B: diclofenac diethylammon group (diclofenac diethylammon gel and sham acupuncture; sham acupuncture is placebo acupuncture); and Group C: placebo group (sham acupuncture and placebo gel) to receive treatments. There will be 20 sessions of treatment in total between weeks 1 and 4, with follow-ups at weeks 8 and 12. Figure 1 shows the flowchart of the trial process, and Table 1 shows the enrollment, treatment, and assessment schedule (Fig. 1 and Table 1).

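### The analysis labelled intention-to-treat is restricted, in the next sentence, to adherent patients who completed follow-up, and removals after randomisation add to the problem

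*Protocol article*

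**What the plan says.** All references are to the protocol article.

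- **Statistical analysis**, on the principle: "Intention-to-treat analysis will be used for outcome measurements to analyze missing values, based on the last observation carried forward method".
- **Statistical analysis**, the next sentence, which opens by tying itself to the handling of missing values: "only patients who attended at least 80% of the sessions and completed the follow-up in the allocated intervention group will be included".
- **Discontinuation criteria and modification**: "Participants who meet the following criteria will be excluded from the trial during the trial period". The criteria include unpermitted co-treatment ("such as taking analgesics without permission or receiving other treatments"), unwillingness ("participants were reluctant to continue treatments") and low attendance ("missing more than 4 of 20 acupuncture treatment sessions").
- **Primary outcome**: "the primary outcome will be the assessment at week 4". **Study design** uses the word follow-up for later visits: "with follow-ups at weeks 8 and 12".

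The article names no separate per-protocol set, and nowhere says that every randomised patient enters the primary comparison.

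**The concern.** The two sentences in Statistical analysis describe the same analysis and point in opposite directions. Intention-to-treat with carried-forward values exists to keep patients who stop or go missing. The restriction removes those same patients. An analyst could follow either sentence and claim to have followed the plan.

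The removal criteria act after randomisation. Taking unpermitted analgesics or losing willingness to continue may reflect how well the allocated treatment works. The burden also differs by arm: needling in Group A goes to 21–26 mm with manipulation to obtain deqi, whereas sham needling goes to 1–2 mm without manipulation. If exclusion relates to response and differs between arms, the patients left are no longer the groups that randomisation made comparable. The resulting bias can favour or disfavour acupuncture. Outcomes that were never collected cannot be recovered at analysis.

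**Working it through.** **1. The two sentences side by side.** The first makes intention-to-treat the analysis of missing values. The second says who enters the analysis of missing values: patients with at least 80% attendance who also completed follow-up. A patient who completed follow-up might still have missed an intermediate visit, so something could be carried forward, but almost nothing.

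**2. The attendance cuts.** 80% of 20 sessions is 0.80 × 20 = 16. Missing more than 4 of 20 means attending at most 15. The two rules use the same cut, so the removal rule and the analysis restriction reinforce each other.

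**3. What completing follow-up means.** The primary assessment is at week 4, and Study design calls weeks 8 and 12 the follow-ups. On that meaning, a patient with an observed week-4 WOMAC who misses week 12 could be dropped from the primary comparison.

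**4. The plan's own sample size.** Inputs from Sample size: reductions of 17, 13 and 10, SD 10.24, two-sided 0.05.
- Grand mean = 40/3 = 13.33. Mean squared deviation = (13.44 + 0.11 + 11.11)/3 = 8.22. Effect size f = √8.22 / 10.24 = 0.280.
- One-way ANOVA with the noncentral F distribution: the smallest n with 80% power is 42 per group (80.03%). The stated figure is reproduced.
- Same means and SD, other set sizes: all 46 per group gives 83.8%; 10% excluded (46 × 0.90 = 41.4, taken as 41) gives 79.0%; 20% excluded (46 × 0.80 = 36.8, taken as 37) gives 74.3%. The loss of power is modest; bias is the larger issue.

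**5. Bias under partial selection (assumed rates and gap).** Let a proportion p of an arm be excluded, and let the excluded improve D points less than the retained. If the whole-arm mean is m, the retained mean is m + pD. The bias in A minus C is therefore (p_A − p_C) × D when D is the same in both arms.

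| Excluded A vs C | D = 5 | D = 10 |
|---|---|---|
| 10% vs 10% | 0 | 0 |
| 15% vs 5% | 0.10 × 5 = 0.5 | 0.10 × 10 = 1.0 |
| 20% vs 5% | 0.15 × 5 = 0.75 | 0.15 × 10 = 1.5 |

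The planned A minus C difference is 17 − 10 = 7, so the largest entry is 1.5/7 = 21% of it. Swapping the arms reverses the sign.

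**6. Worst case (assumed perfect selection, one arm only).** If exactly the worst-responding fraction q of one normal arm is removed, its mean rises by SD × φ(z_q)/(1 − q).
- q = 0.10: 10.24 × 0.1755/0.90 = 2.0 points.
- q = 0.20: 10.24 × 0.2800/0.80 = 3.6 points.

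Removal from C only would shrink the difference of 7 to 5.0 or 3.4. Removal from A only would inflate it to 9.0 or 10.6. In the terms of step 5, these shifts need a gap D of 2.0/0.10 = 20 or 3.58/0.20 = 17.9 points, nearly two standard deviations.

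**7. False-positive rate (simulation).** Assumptions: no true difference, 46 randomised per group, correlation 0.5 between adherence and improvement, 8,000 runs.

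| Excluded A vs B and C | ANOVA type I error |
|---|---|
| 10% vs 10% | 5.2% |
| 15% vs 5% | 6.7% |
| 20% vs 5% | 8.1% |
| 25% vs 5% | 9.9% |

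**The case against.** The restriction opens with a clause confining it to the analysis of missing values, and the ANOVA comparison is described separately without it. It may be a garbled per-protocol definition. This stands as far as it goes: a reader might infer that the primary comparison is definitely a completer analysis, and the text does not settle that. But the preceding sentence makes the missing-value analysis the intention-to-treat analysis, and no other set is named. A fuller analysis plan might define the sets properly, yet the printed contradiction would still need correcting.

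A reader might also infer that the discontinuation section rules out intention-to-treat. It does not. It is silent on whether assessments end, and baseline is taken before the allocation envelope is opened, so all 138 patients have a value to carry forward, however poor that imputation. The fair statement is that the section leaves later outcome collection in doubt.

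It is likewise tempting to say that every exclusion depends on treatment response, or that about half of the planned effect could disappear. Missed sessions can have unrelated causes. The halving needs the worst 20% of one arm, exactly, with nobody removed from the other; nothing in the article supports selection that sharp.

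Finally, counting needling sessions alone might look unfair to Group B, whose active treatment is the gel. The rule is the same in all arms and each arm has 20 needling sessions, so this is a refinement for a sensitivity set.

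**Conclusion.** The contradiction is real and needs correcting. The analysis called intention-to-treat can be read as one of adherent completers, possibly dropping patients whose week-4 outcome was observed, and the removal rule makes that reading more damaging.

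The documents give neither exclusion rates nor any link between exclusion and response, so the bias can only be bracketed:
- zero if exclusion is unrelated to outcome, or if rates and selection are the same in all arms;
- about 0.5 to 1.5 points of the planned 7 under the unequal rates and 5–10 point gap assumed above;
- 2.0 to 3.6 points only in the one-arm, perfect-selection extreme.

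The sample size calculation is not at fault.

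**What to change.** - In Statistical analysis, define the primary set as all randomised patients, analysed in the group to which they were allocated.
- Delete the 80%/completer sentence from that analysis. Keep the rule only as a labelled per-protocol sensitivity analysis, and say which visit completing follow-up refers to.
- Reconcile the discontinuation section with Statistical analysis by stating that stopping treatment does not end outcome assessment: the scales are still collected at weeks 4, 8 and 12 unless consent is withdrawn. The clinical discontinuation criteria stay as they are.

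Whether last observation carried forward is the right method for values still missing is a separate question that this change leaves open.

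The cost is wording in two sections and some extra attempted assessments; no more patients are needed. The number who stop treatment is not given. If it matched the 10% loss allowance (an assumption), it would be about 0.10 × 138 = 14 patients and at most 14 × 3 = 42 assessments. Trial status describes recruitment as not yet begun at the time of writing, so the wording could be settled before anyone is removed.
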